### Sampling frame

Colorectal surgeons in Canada can be identified by membership with the Canadian Society of Colon and Rectal Surgeons (CSCRS). This organization has been contacted and a list of members’ updated emails are maintained and accessible. There are an estimated 114 surgeons registered with CSCRS. Eligible surgeons working specifically with rectal cancer patients will be identified by the first question in the online survey.

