### Instrument

A single survey tool modified from the Facilitators and Barriers Survey by Graham et al. will be used for physicians [49]. The 41 item survey will be divided into five main areas: 1) development of the decision aid; 2) content and format of the decision aid; 3) decision aid and meeting patients’ needs; 4) physicians’ clinical practice; 5) implementation. All questions will be rated on a 5-point scale from 1 (strongly agree) to 5 (strongly disagree). There are two questions asking surgeons how likely they are to use the decision aid, rated as “not at all” to “very likely”. Two questions will explore the additional facilitators and barriers not mentioned in the survey. Two questions will explore program specific adaptation and further comments. This survey tool was first used in a study of 270 physicians in three different specialties and later modified for two subsequent studies of nurses. Using principal component analysis with Verimax rotation, Graham et al. showed factorial validity with survey items loaded on four components including quality and value for patients, value for physicians, decision aid content, and implementation issues [49]. The same survey tool was then adapted and used in studies to assess factors influencing nurses’ use of decision aid in a primary care call center [50] and an Australian cancer call center [51].

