### Statistical analysis

Data will be captured by the online survey software and downloaded to the study database. Response rate will be determined based on the total number of completed, partially completed, refusals and breakoffs, noncontact (failed to deliver), and unknown eligibility. Ineligibility will be determined by the first question on the survey asking respondents to identify whether they are surgeons working with rectal cancer patients. Non-response rate will be reported. Descriptive statistics will be used to generate characteristics of survey respondents. All response distribution will be presented.

The intention question on the physicians’ likelihood of using the decision aid will be dichotomized into a binary variable with ‘likely’ and ‘very likely’ versus the rest of the responses. Intention will be subsequently used as a response variable in a logistic regression model. Principal component analysis with Verimax rotation will be performed on all items to confirm common themes and logistic regression analysis will be used to identify independent variables associated with the intention to use the decision aid. The independent variables will be components extracted from principal component analysis.

Item-missing data will be explored and addressed by casewise deletion, variable deletion, and possibly imputation, depending on its extent and nature. Respondents presenting with more than half missing values will be excluded from analysis.

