## Discussion

Shared decision making is a strategy that is being promoted across the healthcare systems in the US and Canada [52]. Currently the rectal cancer decision aid has been developed, but has not been formally evaluated. This study aims to evaluate the decision aid and explore the perceived barriers and facilitators to the implementation of the decision aid. It will help with planning strategies for designing interventions to facilitate implementation and overcome known barriers to use of the decision aid in routine clinical practice [32].

Physician/nursing/management collaboration will also be a major factor in completing the pre- and post- study. We will hold meetings with surgeons and nursing staff at the Cancer Assessment Centre to increase awareness among staff. Information sheets will be available in the rectal cancer clinics to remind the staff of inclusion & exclusion criteria of the study.

The single arm pre- and post- design of the study and the lack of control and blinding pose threat to our ability to make causal inferences. Nonetheless, important information will be obtained on how the rectal cancer DA may impact the choice and decision-making process of a patient, the acceptability of the decision tool to patients, and the feasibility of integrating this decision aid into everyday practice.

For the survey study, low survey response rate may introduce non-response bias where responders and non-responders are different. Therefore, this study will attempt to maximize response rate by obtaining accurate email addresses, using a simple and concise questionnaire, and sending follow up reminders [48]. Response/non-response will be reported. Discussion of possible bias will be an important part of the interpretation of the findings.

The implementation of the decision aid could lead to more evidence based knowledge dissemination related to rectal cancer and the surgical choices, less uncertainty related to decisions, and ultimately decisions more congruent with patients’ values. To our knowledge this is the first study designed to evaluate a decision aid in the field of colorectal oncology. The data collected from this study could lead to more definitive large scale studies on the surgical decision aid in the future.

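### With a frame of at most about 114 surgeons, the intention-to-use logistic regression should name a penalized (Firth) fit, because at ordinary response rates the default fit overstates real odds ratios on average

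*Protocol article*

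**What the plan says.** The Part 2 Sampling frame section sets the ceiling: "There are an estimated 114 surgeons registered with CSCRS". That number comes before any loss, since "Eligible surgeons working specifically with rectal cancer patients will be identified by the first question in the online survey". The Statistical analysis section also excludes respondents with more than half their values missing and allows casewise deletion.

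The same section fixes the model. The answer on "likelihood of using the decision aid will be dichotomized into a binary variable with" the two upper categories on one side and everything else on the other. Then "logistic regression analysis will be used to identify independent variables associated with the intention to use the decision aid", and "The independent variables will be components extracted from principal component analysis". The number of components is not stated. The Instrument section reports that in an earlier study of 270 physicians "survey items loaded on four components including quality and value for patients, value for physicians, decision aid content, and implementation issues".

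The article states no expected response rate, no expected split on intention, and no fitting method beyond logistic regression. The Discussion mentions low response only as a source of bias: "low survey response rate may introduce non-response bias where responders and non-responders are different".

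**The concern.** Intention to implement the aid is the primary outcome of Part 2, and the regression is where the factors affecting it are to be identified. What limits a logistic model is the number of subjects in the smaller outcome group relative to the number of coefficients. With a ceiling of about 114 and several components, that ratio is low at any ordinary response rate. Fitted in the usual way, by maximum likelihood, such a model pushes non-null coefficients away from zero on average, sometimes gives very large odds ratios, and can fail outright when a component separates the two groups. A reader planning an implementation strategy could then take a real but moderate association for a strong one.

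**Working it through.** Part 2 contains no sample-size or precision figure, so there is none of the plan's own to reproduce. The check has three steps.

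**1. Surgeons per component.**

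Inputs from the article: frame 114; four components in the earlier physician study. Assumptions: all eligible; response 40-60%; 50-80% likely to use, so the smaller group is 20-50% of respondents.

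Formula: frame × response × smaller-group share ÷ number of components.

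- Respondents: 114 × 0.40 = 45.6, about 46; 114 × 0.60 = 68.4, about 68.
- Lowest: 46 × 0.20 ÷ 4 = 2.3 per component.
- Highest: 68 × 0.50 ÷ 4 = 8.5 per component.
- Ceiling, all 114 eligible and answering: 114 × 0.50 ÷ 4 = 14.2 with an even split; 114 × 0.20 ÷ 4 = 5.7 with a 20% smaller group.

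Only near-full response with a near-even split takes the ratio above 10. If 80% are eligible, every figure falls by a fifth.

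**2. Bias at the assumed response.**

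Surveys were simulated with four components and a true odds ratio of 2.0 per SD on the non-null ones. Average odds ratios are the exponentiated mean log odds ratio.

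| Respondents | Maximum likelihood, average OR | Above 4 | Firth, average OR | Above 4 |
|---|---|---|---|---|
| 46-68, 50-80% likely to use | about 2.2-2.45 | about 5-17% | about 2.0 | 2-8% |
| 114 | 2.11-2.14 | – | about 2.0 | – |

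Firth also had the lower root mean squared error in every setting. The bias does not depend on a lopsided split: it is present with 50/50 as well.

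**3. A second data model, with a wider range.**

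Here one component has a true odds ratio of 2.0, each of the other three has a log odds ratio of 0.3, and there are 600 surveys per row. The Firth column is 2 raised to the ratio of the mean Firth log odds ratio to the truth; for example, a ratio of 1.06 gives 2^1.06 = 2.08.

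| Respondents | Smaller group | Per component | ML average OR | Firth average OR | Failed ML fits | SD of ML log OR |
|---|---|---|---|---|---|---|
| 114 | 50% | 14.2 | 2.15 | 2.06 | 0% | 0.25 |
| 114 | 20% | 5.7 | 2.13 | 2.01 | 0% | 0.30 |
| 57 | 50% | 7.1 | 2.20 | 2.00 | 0% | 0.41 |
| 57 | 30% | 4.3 | 2.23 | 2.00 | 0% | 0.45 |
| 57 | 20% | 2.9 | 2.41 | 2.08 | 0.2% | 0.55 |
| 34 | 30% | 2.6 | 2.65 | 2.04 | 0.2% | 0.88 |
| 34 | 20% | 1.7 | 2.98 | 2.10 | 2.8% | 1.16 |

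With a 10% smaller group, failed fits reach 3.5% at 57 respondents and 25% at 34.

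**Bias against imprecision**, at 57 respondents:

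- 30% smaller group: ln 2.23 − ln 2.00 = 0.802 − 0.693 = 0.109, which is 0.109 ÷ 0.45 = 0.24 SD.
- 20% smaller group: ln 2.41 − ln 2.00 = 0.880 − 0.693 = 0.187, which is 0.187 ÷ 0.55 = 0.34 SD.

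Sampling spread is therefore three to four times the bias. At SD 0.45, about 95% of estimates lie within a factor of exp(1.96 × 0.45) = 2.4 of their centre in either direction.

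**The case against.** Four points can be made against this.

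**Estimator detail belongs in a fuller plan.** The article says only logistic regression, and Firth's method is one way of fitting it. This is fair, and the article is not wrong on its face. But it does fix the frame, the binary outcome and the type of predictor, and that combination is where the default fit does poorly. Naming the method is a modest addition.

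**The size rests on assumptions.** A reader might infer that the smaller intention group is bound to be tiny and the odds ratios bound to be inflated. The article supports neither, because it gives no response rate and no split. With all 114 answering and an even split, the smaller group holds 57 surgeons and the bias is mild. The average is also pulled up by near-separated surveys: at 46-68 respondents with 70-80% likely to use and four or five components, the median maximum-likelihood estimate was 2.11-2.34.

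**The ranking is not harmed.** A reader might infer that inflated odds ratios would misorder the barriers or make irrelevant ones look important. Simulation does not bear this out. The two truly associated components came out on top about equally often under both methods (in one comparison 57.5% against 58.1%). A null component is not pushed in one direction; ordinary Wald tests flagged it in 3.3-5.2% of surveys. Misordering comes from imprecision, which a penalized fit largely leaves in place.

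**The purpose is exploratory.** The Study objectives section speaks of exploring surgeons' views, and the Discussion looks ahead to larger studies. This lowers the stakes, and it argues for labelling the odds ratios accordingly.

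**Conclusion.** The point holds as a conditional, low-cost improvement. If 40-60% of the frame responds, 50-80% are likely to use the aid and four components are entered, ordinary maximum likelihood would on average report a true odds ratio of 2.0 as about 2.2-2.45 and exceed 4 in about 5-17% of surveys. Firth's fit would report about 2.0 and exceed 4 in 2-8%. Lower response, a more lopsided split or more components make it worse; full response reduces it to about 2.1. Only the ceiling of 114 and the form of the model come from the article; response, split and eligibility are assumptions, and four components is carried over from the earlier study.

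What is at stake is the size of real associations, a share of extreme estimates and an occasional failed fit. Neither the ordering of components nor false signals from null ones is at issue, and wide intervals will limit interpretation under either method.

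**What to change.** In the Part 2 Statistical analysis section, state that the logistic model will be fitted by Firth's penalized likelihood, with profile-likelihood confidence intervals, and that the odds ratios are exploratory.

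The cost is one sentence and one analysis option, with no extra data. Where the smaller group is large, the results barely differ. The downsides are slightly shrunken estimates and output that some readers will find less familiar. The change removes most of the bias and gives finite estimates under separation, but it does not narrow the uncertainty much, so the intervals should be shown with every odds ratio.

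Fixing the predictors at the four earlier components is not part of this recommendation: the article describes the survey tool as modified, so whether that structure carries over is open.

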## Discussion

Shared decision making is a strategy that is being promoted across the healthcare systems in the US and Canada [52]. Currently the rectal cancer decision aid has been developed, but has not been formally evaluated. This study aims to evaluate the decision aid and explore the perceived barriers and facilitators to the implementation of the decision aid. It will help with planning strategies for designing interventions to facilitate implementation and overcome known barriers to use of the decision aid in routine clinical practice [32].

Physician/nursing/management collaboration will also be a major factor in completing the pre- and post- study. We will hold meetings with surgeons and nursing staff at the Cancer Assessment Centre to increase awareness among staff. Information sheets will be available in the rectal cancer clinics to remind the staff of inclusion & exclusion criteria of the study.

The single arm pre- and post- design of the study and the lack of control and blinding pose threat to our ability to make causal inferences. Nonetheless, important information will be obtained on how the rectal cancer DA may impact the choice and decision-making process of a patient, the acceptability of the decision tool to patients, and the feasibility of integrating this decision aid into everyday practice.

For the survey study, low survey response rate may introduce non-response bias where responders and non-responders are different. Therefore, this study will attempt to maximize response rate by obtaining accurate email addresses, using a simple and concise questionnaire, and sending follow up reminders [48]. Response/non-response will be reported. Discussion of possible bias will be an important part of the interpretation of the findings.

The implementation of the decision aid could lead to more evidence based knowledge dissemination related to rectal cancer and the surgical choices, less uncertainty related to decisions, and ultimately decisions more congruent with patients’ values. To our knowledge this is the first study designed to evaluate a decision aid in the field of colorectal oncology. The data collected from this study could lead to more definitive large scale studies on the surgical decision aid in the future.
